### Process evaluation

A key study objective is to understand lessons for the scale-up of community-based deworming in Kenya and elsewhere in Africa. Therefore, a qualitative evaluation will seek to identify and describe key assumptions and conditions underlying the implementation, sustainability and scaling-up of the different strategies and delivery systems. The focus of the evaluation will centre on whether CHVs can be utilised for the effective delivery of chemotherapy for control of STH and what factors influence the use of CHVs, including what type of incentives, if any, should be given. Investigation will focus on: (1) community acceptability, which will be assessed during FGDs and in-depth interviews (IDIs); and (2) feasibility, including a situation and stakeholder analysis of the structural, organisational and management factors that enhance or constrain effective implementation.^42^ A series of FGDs will be conducted with community members, teachers, CHVs, CHEWs and local health officials, to better understand the acceptance and implementation of the interventions, using predefined and structured topic guides. FGDs will be stratified by location and socioeconomic status, and specific efforts will be made to reach groups that may be marginalised due to their economic and sociocultural position. IDIs will be carried out with a range of actors and opinion leaders in order to understand the process and constraints of the different delivery systems. The number of IDIs will depend on when saturation is reached, but they will include members of the county, and national health and education teams.

FGDs and interviews will be digitally recorded, with notes additionally taken, transcribed and translated. Transcripts will be imported into NVivo (QSR International, Doncaster, Australia), coded by two independent coders, and analysed using content analysis to identify emerging themes.^43^ Following descriptive analysis, patterns and linkages among views, experiences and behaviours of the participants will be explored. The collected data will provide important contextual information and a basis for evaluating the generalisability of the study findings. The work will benefit from previous qualitative evaluations by the research teams in the study areas.^44–47^

### Cost analysis

Cost data will be collected following an ingredients approach, based on a semistructured questionnaire and by consultation of the programme accounting system. Data collection will be based on a standardised costing framework, capturing fixed and recurrent costs incurred at school and community levels. The questionnaire will include both cash and in-kind contributions, and will be used to estimate financial and economic costs of the alternative treatment strategies (annual vs biannual deworming) and delivery systems (through schools by teachers and through door-to-door delivery by CHVs). Financial costs capture actual expenditures in terms of programme implementation, whereas economic costs include opportunity costs of teachers, CHVs and other stakeholders in delivering deworming. Opportunity costs of the government staff and community members will be calculated using local pay scales. Capital costs will be annuitised over the useful life of equipment, vehicles and other assets using a discount rate of 3%. Costs will be assessed from a societal perspective. Analysis of costs will be linked to volume of treatment in order to determine cost functions. The work will also present an analysis of the full cost of running national programmes in Kenya. Itemised-costing and sensitivity analysis will enable estimation of the costs of scaled-up implementation, and implementation in settings with different epidemiological and programmatic characteristics.

### Mathematical modelling and cost-effectiveness analysis

The questions being addressed in the trial arose from analyses of the predicted impact of mass treatment based on mathematical models of the transmission dynamics and control of STHs.^9–11^
^48^ The potential for transmission of STHs and other helminths in a defined setting can be quantified by the value of the basic reproductive number (R_0_), which is defined as the average number of offspring produced by one female worm that survives to reproductive maturity. R_0_ can be stratified by age (age-related exposure), and various environmental and behavioural factors.^49^ In endemic communities, mathematical models of helminths that are dioecious have two stable points (no parasites and a stable endemic equilibrium of parasite persistence), separated by an unstable point—the so called ‘breakpoint’ in transmission (a point at which R_0_ falls to just above but close to unity (1) in value), below which continued treatment can quickly drive the population to extinction. For attempts at elimination, the goal of mass treatment is to drive the parasite population below the ‘breakpoint’ by treating sufficient fractions of the target population. Models of STH transmission provide insight into optimal treatment strategies for achieving this breakpoint,^9^
^10^ and show that annual or biannual community-based deworming can reduce overall prevalence and associated intensity substantially. As an example, reaching the transmission breakpoint can be achieved after 2 years given a baseline prevalence of 10% or less (low transmission setting) if coverage is high. The models also highlight how the age-distribution of worm burden determines the breadth of age groups that should be treated and the importance of considering the species mix.

Data arising from the trials will be used to validate the initial model predictions and to provide better estimates of key epidemiological parameters for use in model predictions. Specifically, the study will produce better estimates of the following parameters: density dependent fecundity, parasite distributions in the various age groupings (estimates of the negative binomial aggregation parameter k), age dependent exposure to infection, drug efficacy and treatment compliance. The models will be fitted with estimates of age-stratified patterns of reinfection and intensity of infection, as well as estimates of treatment coverage using Monte Carlo Markov Chain methods. Such model fitting and parameter estimation will allow examination of whether the observed and predicted impact is consistent. A stochastic model of STH transmission is also under development to enable estimates of variability around deterministic predictions (such as time to crossing the breakpoint) to be made taking account of the many heterogeneities involved in parasite transmission.

The models will be used to explore the impact of the different treatment strategies in a range of settings, with different underlying intensity in levels of transmission and treatment coverage, and the potential impact of alterations (in coverage and frequency) to the treatment strategies over time. The duration of treatment required to cross the ‘breakpoint’ in transmission will also be examined. Particular attention will be given to non-compliers to treatment (both persistent and irregular) in all study groups, and work will examine the impact on overall transmission of poor adherence to treatment.

The cost data, detailed above, will be integrated into the models for cost-effectiveness analysis. The incremental costs per infection, heavy infection, anaemia case and disability adjusted life years averted will be estimated for the two new strategies compared to the current situation with annual school-based deworming. Sensitivity analysis will be undertaken to account for uncertainties in the analysis, with attention given to the impact of non-compliance.

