## Abstract

**Introduction:**

In recent years, an unprecedented emphasis has been given to the control of neglected tropical diseases, including soil-transmitted helminths (STHs). The mainstay of STH control is school-based deworming (SBD), but mathematical modelling has shown that in all but very low transmission settings, SBD is unlikely to interrupt transmission, and that new treatment strategies are required. This study seeks to answer the question: is it possible to interrupt the transmission of STH, and, if so, what is the most cost-effective treatment strategy and delivery system to achieve this goal?

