**Methods and analysis:**

Two cluster randomised trials are being implemented in contrasting settings in Kenya. The interventions are annual mass anthelmintic treatment delivered to preschool- and school-aged children, as part of a national SBD programme, or to entire communities, delivered by community health workers. Allocation to study group is by cluster, using predefined units used in public health provision—termed community units (CUs). CUs are randomised to one of three groups: receiving either (1) annual SBD; (2) annual community-based deworming (CBD); or (3) biannual CBD. The primary outcome measure is the prevalence of hookworm infection, assessed by four cross-sectional surveys. Secondary outcomes are prevalence of *Ascaris lumbricoides* and *Trichuris trichiura*, intensity of species infections and treatment coverage. Costs and cost-effectiveness will be evaluated. Among a random subsample of participants, worm burden and proportion of unfertilised eggs will be assessed longitudinally. A nested process evaluation, using semistructured interviews, focus group discussions and a stakeholder analysis, will investigate the community acceptability, feasibility and scale-up of each delivery system.

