### Aims and objectives

The overall aim of the trials is to evaluate the impact and cost-effectiveness of school-based versus community-based deworming on measures of STH transmission in Kenya. Specifically, we will test the hypothesis that treatment needs to be provided to a broad range of ages and/or at more frequent intervals than 1 year in order to interrupt the transmission of STH. The study also includes process and economic evaluations to assess the feasibility and implementation of the alternative treatment strategies and delivery systems, which will guide scale-up of the programmes in Kenya and other settings in Africa. The more detailed study objectives are:
To quantify the impact of school-based versus community-based mass treatment (treatment strategies and delivery systems) at annual and biannual intervals (treatment strategies) in reducing the transmission of STH spp, hookworm, *A. lumbricoides* and *T. trichiura*.To evaluate the costs and cost-effectiveness of alternative STH treatment strategies and delivery systems in reducing transmission.To assess the extent to which community-based treatment programmes for STH are acceptable to the community, which are feasible, given the health system capacity, and can be easily scaled-up across Kenya and elsewhere.

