### Data analysis

Primary analysis will be carried out on groups as randomised (intention-to-treat). Results will be presented as appropriate effects sizes with a measure of precision (95% CIs). Clustering by CU will be included in all analyses. Our main analysis of the primary outcome, the prevalence of hookworm, and other secondary outcomes, will be based on cross-sectional analyses comparing the outcome at 30 months follow-up between study groups. Unadjusted and adjusted results will be presented for all analyses. Covariates in adjusted analyses will be specified a priori and will include subcounty and urban/rural classification, household socioeconomic status, and access to adequate water and sanitation. For continuous outcomes, analyses will adjust for baseline by inclusion of the cluster mean of the outcome in question as a covariate in statistical models. For binary outcomes (notably the primary outcome), no baseline adjustment will be made because of issues relating to the non-collapsibility of ORs.

Demographic and other baseline characteristics of clusters will be compared to check for imbalances between study groups. Tabulation of these measures will be generated using the intention to treat data sets. No significance tests will be performed to investigate for differences between groups at baseline. Where imbalances are suspected, further exploratory adjusted analyses will be carried out that include additional adjustment for these factors. Formal statistical testing will be restricted to comparison between the two community-based treatment groups and the school-based treatment group (control). A small number of secondary outcomes will be prespecified for statistical testing along with the primary outcome. No formal adjustment will be made for multiple testing but the number of outcomes formally tested will be restricted to fewer than 10 and the results interpreted with due caution. This includes multiplicity associated with the two experimental arms. No formal comparisons will be made between the two experimental arms as the study has not been powered for this analysis.

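### Annual school-based deworming is the only comparator named for the incremental cost-effectiveness ratios of both new strategies, so the planned ratios do not show the incremental cost of the second community round

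*Protocol article*

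**What the plan says.** The Abstract's Introduction sets the question: if interruption is possible, "what is the most cost-effective treatment strategy and delivery system to achieve this goal". The Abstract's Methods paragraph lists the options, with community units "receiving either (1) annual SBD; (2) annual community-based deworming (CBD); or (3) biannual CBD". The second objective under Aims and objectives is general: "To evaluate the costs and cost-effectiveness of alternative STH treatment strategies and delivery systems in reducing transmission". It fixes no comparator.

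The comparator appears in Mathematical modelling and cost-effectiveness analysis. "The incremental costs per infection, heavy infection, anaemia case and disability adjusted life years averted" are the ratios, and they "will be estimated for the two new strategies compared to the current situation with annual school-based deworming". No section names a ratio of biannual over annual community treatment, or a ranking of the three strategies.

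Three other statements bear on this:

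- Cost analysis will "estimate financial and economic costs of the alternative treatment strategies (annual vs biannual deworming) and delivery systems".
- The models will explore "the potential impact of alterations (in coverage and frequency) to the treatment strategies over time".
- Data analysis states: "No formal comparisons will be made between the two experimental arms as the study has not been powered for this analysis".

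**The concern.** A community unit receives one of three strategies, and under Overall study design the third is the second plus one further community round six months later. Choosing among mutually exclusive options by incremental ratios means comparing each option with the next less costly one that is not dominated. The plan instead measures both new strategies from the same starting point.

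The ratio for biannual community treatment against school-based deworming then blends two steps: extending treatment to the community at all, and adding the second round. A favourable first step can carry an expensive second one. A policymaker who sees only the two planned ratios could accept biannual treatment although the second round costs more per unit of benefit than they would pay. The reverse error is also possible: the step from annual to biannual could be good value without the reader being shown it.

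**Working it through.** **Inputs.** The article gives no costs, effects or ratios, so there is no figure of the plan's own to reproduce. What it supplies is the structure: three strategies, one comparator for the ratios, and separate costing of annual and biannual deworming. All costs and effects below are assumed, in arbitrary units.

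**Formulas.** Let dC1 and dE1 be the extra cost and infections averted for annual community treatment against school-based deworming, and dC2 and dE2 the same for biannual.

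- Planned ratios: dC1/dE1 and dC2/dE2.
- Ratio for the second round: (dC2 − dC1)/(dE2 − dE1).

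**Base illustration.** Take dC1 = 100, dE1 = 50, dC2 = 200, dE2 = 60.

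- Annual against school-based: 100/50 = 2.0.
- Biannual against school-based: 200/60 = 3.33.
- Biannual over annual: (200 − 100)/(60 − 50) = 10.

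The planned biannual ratio is an effect-weighted average of the two steps: (50 × 2.0 + 10 × 10)/60 = 3.33. At any willingness to pay between 3.33 and 10, biannual treatment looks acceptable against school-based deworming while the second round costs more than that amount.

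**Range.** Costs are held at 100 and 200 and dE1 at 50; only dE2 varies.

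| dE2 | Biannual vs school-based | Biannual vs annual community |
|---|---|---|
| 55 | 200/55 = 3.64 | 100/5 = 20 |
| 60 | 200/60 = 3.33 | 100/10 = 10 |
| 80 | 200/80 = 2.50 | 100/30 = 3.33 |
| 100 | 200/100 = 2.00 | 100/50 = 2.00 |
| 120 | 200/120 = 1.67 | 100/70 = 1.43 |

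The planned ratio is too low for the second round when effect grows less than in proportion to cost. The two agree when effect doubles with cost. In the last row the step to biannual (1.43) is cheaper per infection averted than the step to annual (2.0). Annual community treatment is then extendedly dominated, and the correct ratio for biannual is 1.67, against school-based deworming, as planned.

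**Can the reader recover the missing ratio?** From the increments, yes. From the two ratios alone, no. Doubling both biannual increments to 400 and 120 leaves the planned pair at 2.0 and 3.33, but the ratio for the second round becomes (400 − 100)/(120 − 50) = 4.29 instead of 10.

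**The case against.** The article condenses a fuller plan. It rules nothing out, and ranking and dominance rules are details that such an article often leaves elsewhere. That would be decisive if the text were silent. It is not: it names a comparator for both new strategies, and that choice does not fit the question in the Abstract.

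A reader might go further and infer that the strategies are costed only against school-based deworming, or that the comparison of biannual with annual community treatment will never be made. The documents support neither. Cost analysis costs annual and biannual deworming as separate strategies, the models vary treatment frequency, and the missing ratio follows arithmetically from increments that the plan will produce.

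Nor does the bar in Data analysis on comparing the two experimental arms settle the matter. It concerns formal testing and gives lack of power as the reason, so a modelled ratio remains open. It does carry a fair warning: dE2 − dE1 may be small and imprecise, which makes the ratio unstable.

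The strongest objection concerns direction. Understatement needs diminishing returns. Those are plausible, since prevalence cannot fall below zero and the sample size section starts from 5% to 10%, but nothing in the article establishes them. The modelling section rests on a transmission breakpoint, and the Introduction links interruption to treating adults and treating more often, so increasing returns are also conceivable. This objection stands in full. It limits the claim to a conditional one, but it also shows why the analysis should find out which case applies.

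Finally, the Abstract's question turns first on which strategies interrupt transmission, and cost per infection averted does not settle that alone. This is true, but the article still chooses these ratios as its cost-effectiveness measures.

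**Conclusion.** The point holds in a limited form. The stated ratios share one comparator, and two such ratios are not enough to identify the most cost-effective of three mutually exclusive strategies. How much this matters depends on quantities that the article does not give. In the assumed cases the ratio for the second round runs from 20 against a planned 3.64, through equality at 2.00, to 1.43 where the planned 1.67 is the correct figure. A general claim that the plan underprices biannual treatment is therefore not supported; it does so only under diminishing returns.

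The illustration assumes that costs rise from school-based to annual to biannual community treatment, which is natural when each adds to the one before but is not documented. The randomisation, primary outcome, sample size and main analysis are unaffected. This is a moderate improvement to the economic analysis and not a must-fix.

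**What to change.** In Mathematical modelling and cost-effectiveness analysis, add wording such as: *A fully incremental analysis of the three strategies will be done for each effect measure. Strategies will be ranked by cost, dominated and extendedly dominated strategies removed, and each remaining strategy compared with the next less costly one. Uncertainty will be taken jointly from the model outputs for all three strategies. Ratios against annual school-based deworming will be reported alongside.*

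Add one sentence that the comparison of biannual with annual community treatment is estimation and not a formal test, because the trial is not powered for it, and that costs and effects for each strategy will be shown as well as ratios.

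The cost is small: some extra analysis on costs and modelled effects already planned, and no new data. The downside is that the ratio of biannual over annual community treatment may be imprecise. Reporting it with its uncertainty deals with that better than leaving it out.

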## Ethics and dissemination

### Ethical approval

The study has been approved by the Kenya Medical Research Institute and National Ethics Review Committee (SSC Number 2826) and the London School of Hygiene and Tropical Medicine (LSHTM) Ethics Committee (7177). Sponsorship and insurance is provided by the LSHTM's Clinical Trials Sub-Committee (QA615).

### Informed consent

The study is intentionally embedded within the ongoing NSBDP, which will continue to deliver deworming to all schools in the study areas. At the time of household visits, household members are asked to give their verbal consent for their participation in the community-based deworming. Written informed consent is obtained from adults and parents or guardians of children, before enrolment in the cross-sectional surveys and longitudinal surveys. Written informed consent will also be sought from individuals included in the qualitative evaluations, including FGDs and in-depth interviews. Participants of FGDs and interviews will be provided the options not to be quoted in any reporting of findings. Study information sheets are provided in English, Kiswahili, Mijikenda, Luhya or Bukusu. Translated documents were verified through back-translation into English. Written assent to participate in the cross-sectional and longitudinal studies is obtained from children aged 13 years and above.

Risks and benefits of participating in the study are presented during community meetings and any issues arising discussed. The risk of participating in the trial is very low. The study drug, albendazole, is extremely safe and no severe adverse events are expected.^50^ In the unlikely situation of events occurring, these will be reported to the study site investigator and the principal will inform the ethics committee. Collection of stool samples is a routine procedure and is considered not to be a medical risk; there is the possibility of embarrassment, which will be minimised by appropriate action.

All information will remain confidential. Laboratory specimens, reports, data collection, and process and administrative forms will be identified by a coded unique identifier to maintain participant confidentiality. Access to collected data will initially be limited to fieldworkers at the point of data collection, and to the study statistician and investigators during analysis. As indicated below, data that are considered non-sensitive and do not include identifying participant information will be made publicly available once the main findings have been published, subject to appropriate data sharing agreements.

